## Abstract

**Background::**

Diabetic nephropathy (DN) is a common microvascular complication of diabetes, which poses a serious threat to the health and life of patients. There is evidence that both α lipoic acid and olmesartan medoxomil have positive effects in the treatment of DN, but whether the 2 have synergistic effects and the effects on blood glucose and oxidation indicators are controversial.

**Methods::**

This is a prospective parallel, randomized, double-blind, placebo-controlled trial to study the effects of α lipoic acid in combination with olmesartan medoxomil on blood glucose and oxidation indicators in patients with DN. Participants will be randomly assigned to a treatment group, which will receive α lipoic acid dispersive tablets combined with olmesartan medoxomil tablets, or a control group, which will receive olmesartan medoxomil tablets combined with placebo for 4 weeks, followed up for 12 weeks. Observation indicators include: glycemic indicators [fasting blood glucose, 2 hours postprandial blood glucose and glycosylated hemoglobin], the oxidation indicators [serum glutathione, superoxide dismutase, malondialdehyde, 8-hydroxydeox-yguanosine], and adverse reactions. Finally, SPASS 22.0 software will be used for statistical analysis of the data.

**Discussion::**

This study will evaluate the effects of α lipoic acid combined with olmesartan medoxomil on blood glucose and oxidation indicators in patients with DN. The results of this study will provide a reference for the clinical use of α lipoic acid combined with olmesartan medoxomil in the treatment of DN.

**Trial registration::**

OSF Registration number: DOI 10.17605/OSF.IO/VJWXS

## Introduction

1

The incidence of diabetes is increasing year by year. According to the statistics of the International Diabetes Federation, there are about 415 million people with diabetes in the world at present, and the number of diabetes patients is expected to reach 642 million by 2040.^[1]^ Diabetic nephropathy (DN) is a renal structural change and abnormal function caused by chronic diabetic microangiopathy. About 30% to 40% of diabetic patients will develop into DN.^[2]^ If DN is not treated in time, it will lead to renal failure and ultimately rely on kidney dialysis to maintain life.^[3]^ Some studies have found that the 5-year survival rate of patients with end-stage renal disease is less than 20%.^[4]^

The generation of DN is not only related to glucose metabolism, but also closely related to oxidative stress.^[5]^ The main mechanism of DN is oxidative stress response caused by inflammation caused by hyperglycemia,^[6]^ and experimental studies have also confirmed the role of oxidative stress in the occurrence and progression of DN.^[7]^ At present, the treatment of DN mainly focuses on controlling blood glucose, improving oxidative stress response and controlling proteinuria. Early treatment to avoid further kidney damage is particularly important for DN patients.^[8–10]^

α lipoic acid is a strong antioxidant, which can improve the antioxidant capacity of the body and inhibit lipid peroxidation in vivo, thus protecting the vascular endothelium and preventing and alleviating the occurrence and progression of DN.^[11]^ Clinical studies have confirmed that lipoic acid injection can effectively reduce the level of oxidative stress, blood glucose and blood lipids in DN patients, and improve the renal function of patients.^[4]^ Olmesartan medoxomil is an angiotensin II receptor antagonist, which can delay glomerulosclerosis, reduce the release of inflammatory factors, prevent and reduce the production of urinary protein, and has a protective effect on the kidney.^[12]^ At present, some scholars recommend the combination of the 2 drugs, and believe that the 2 drugs have a synergistic effect. Some clinical studies have also confirmed that α lipoic acid combined with olmesartan medoxomil can improve the blood glucose level of DN patients, reduce blood glucose fluctuations, relieve the body's oxidative response, and reduce inflammation.^[13]^ However, there is still a lack of rigorous randomized controlled studies to verify these conclusions. Therefore, this study will investigate the effects of α lipoic acid combined with olmesartan medoxomil on blood glucose and oxidation indicators in DN patients through a prospective parallel, randomized, double-blind, placebo-controlled trial.

## Materials and methods

2

### Study design

2.1

This is a prospective, randomized, double-blind, placebo-controlled study of α lipoic acid in combination with olmesartan medoxomil on blood glucose and oxidation indicators in patients with DN. Participants will be randomly assigned to either a treatment group receiving olmesartan medoxomil tablets in combination with alpha lipoic acid dispersive tablets or a control group receiving olmesartan medoxomil tablets in combination with placebo for 4 weeks and followed up for 12 weeks, see Figure 1 for flow diagram and Table 1 for study schedule. This protocol followed the latest Consolidated Standards of Reporting Trials and Standard Protocol Items: Recommendations for Interventional Trials 2013 statement.

**Figure 1 F1:**
[figure not shown]
Flow diagram.

**Table 1 T1:** Study schedule.

	Screening period	Treatment period		Follow-up		
Stage Project	Baseline	2-week	4-week	4-week	8-week	12-week
Record fill	√					
Fulfill inclusion criteria and exclusion criteria	√					
Sign informed consent	√					
Random allocation	√					
Treatment	√	√	√			
Effectiveness observation						
Fasting blood glucose (FBG)	√		√			√
2 h postprandial blood glucose	√		√			√
Glycosylated hemoglobin (HbA1c)	√		√			√
Glutathione (GSH)	√		√			√
Superoxide dismutase (SOD)	√		√			√
Malondialdehyde (MDA)	√		√			√
8-hydroxydeox-yguanosine (8-OHdG)	√		√			√
Safety evaluation						
Blood test and urinalysis	√		√			√
Liver and kidney function	√		√			√
Record of adverse event		√	√	√	√	√

### Ethics and registration

2.2

This Research protocol will be conducted in accordance with the Declaration of Helsinki and Ethical Guidelines for Clinical Research. This study has been approved by our Clinical Research Ethics Committee and registered with the Open Science Framework (registration number: DOI 10.17605/OSF.IO/VJWXS). Before randomization, all patients will be required to sign an informed consent form, giving them the option of continuing the trial at any time.

### Patients

2.3

#### Diagnosis basis

2.3.1

The diagnostic criteria for DN refer to the report from an American Diabetes Association Consensus Conference in 2014.^[14]^

#### Inclusion criteria

2.3.2

1.Meet the diagnostic criteria of DN;2.Age ≥18 and ≤70 years old;3.Subjects agree to participate in this study and sign informed consent.

#### Exclusion criteria

2.3.3

1.primary kidney disease or renal failure caused by other diseases;2.complicated with functional impairment of heart, brain, liver, and other important organs;3.patients with acute or chronic infection;4.women who are pregnant, preparing for pregnancy or breastfeeding;5.patients who are allergic to drugs used in the study;6.patients have serious mental illness or cannot cooperate with the researcher;7.those who have participated in or are currently participating in other clinical trials within the past 1 month.

For patients who drop out of the trial or lost to follow-up, researchers should actively take measures to complete the last test as far as possible, so as to analyze the efficacy and safety of the test and take corresponding treatment measures. All cases of detachment should be recorded on the case report form (CRF), fill in the cause of case shedding.

### Sample size

2.4

The sample size is estimated based on the mean and standard deviation of fasting blood glucose scores after 4 weeks of treatment, which were 5.97 ± 1.82 in the treatment group and 7.28 ± 2.34 in the control group referring to the pre-experiment results. Set α = 0.025, unilateral test, β = 0.20. The PASS15.0 software calculated those 42 participants were required for each group, with an estimated drop-out rate of 10%, and 47 patients would be enrolled in each group.

### Randomization and blinding

2.5

We will use a centralized network-based randomization tool to randomly assign patients who meet the criteria to treatment or control at a ratio of 1:1. Random sequences will be generated using SAS 9.3 software (SAS Institute, Cary, NC) by independent statisticians not involved in trial implementation or statistical analysis. The research assistant will enter patient information on a tablet computer and be assigned a random number to complete the random assignment. The outcome of the assignment is unknown to the patients and principal investigator throughout the study.

### Interventions

2.6

All patients will receive the same basic care, including a low-salt, low-fat diabetic diet, moderate exercise, and control of blood sugar and blood pressure.^[13]^ All of these basic treatments will be detailed on the patient's medical record and CRF.

Treatment group: α lipoic acid dispersive tablets (Tonghe Pharmaceutical Co., LTD., Jiangsu, China, 0.1 g/ tablet), 2 tablets each time, 3 times a day, orally; Olmesartan medoxomil tablet (Wansheng Pharmaceutical Co., LTD., Beijing, China, 20 mg/ tablet); 1 tablet each time, once a day, orally. It lasts for 4 weeks.

Control group: Olmesartan medoxomil tablets (Wansheng Pharmaceutical Co., LTD., Beijing, China, 20 mg/ tablet); 1 tablet each time, once a day, orally; Placebo (mainly composed of starch and dextrin), which has the same shape, size and color as alpha lipoic acid dispersive tablets, prepared and provided by Jiangsu Famai Sheng Medical Technology Co., LTD., China. 2 tablets each time, 3 times a day, orally; It lasts for 4 weeks.

### Outcomes

2.7

1.Blood glucose indicators: fasting venous blood of the patients will be collected early in the morning before and after the treatment, and automatic biochemical analyzer (HITEC-7100, Japan) will be used to measure the blood glucose indicators of the patients, including fasting blood glucose, 2 hours postprandial blood glucose and glycosylated hemoglobin.2.Oxidation indicators: we will use the radioimmunoprecipitation kit (Hengyuan Biotechnology Co., LTD., Shanghai, China) to detect serum glutathione, superoxide dismutase, malondialdehyde, and 8-hydroxydeox-yguanosine.Two research assistants will be responsible for data collection. During the follow-up period, the research assistants will collect data information based on the above indicators at week 4 and week 12 after treatment.

### Safety evaluation

2.8

Patients’ blood routine, urine routine, liver function, kidney function and electrocardiogram will be tested at baseline and after treatment to assess the safety of treatment. Details of all adverse events will be recorded in the CRF, including the time, extent and duration of occurrence, suspected reasons, effective measures and outcomes. After treatment, the incidence of adverse reactions in the 2 groups will be analyzed.

### Data management and quality control

2.9

Any modification or change to the protocol will be re-approved through the formal procedures of our Ethics Committee. Independent clinical research assistants will periodically review research progress. Study data will be collected and recorded in CRF by trained investigators. To ensure data reliability, personal information about potential and registered participants will be collected, shared and kept in a separate repository to protect confidentiality before, during and after the trial. Access to the database will be restricted to the researchers in the research team. Participants’ information will not be disclosed or shared without their written permission.

### Statistical analysis

2.10

The collected data will be statistically analyzed by SPSS 22.0 software. Chi-Squared test will be used for counting data. Mean ± standard deviation ($\bar{x}$ ± S) will be used for measurement data, independent sample *T* test will be used for normal distribution, and Mann–Whitney *U* test will be used for skewness distribution. The difference is considered statistically significant when *P* < .05.

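### The named comparison is unadjusted for baseline although baseline is measured for all seven indicators: valid and adequately powered, but it gives up precision, and the distribution-dependent test leaves the target quantity open

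*Protocol article*

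**What the plan says.** Section 2.10 (Statistical analysis) gives one rule for continuous data: "independent sample *T* test will be used for normal distribution, and Mann–Whitney *U* test will be used for skewness distribution". Continuous data are summarised as mean and SD, and significance is declared at P < .05. No covariate, change score, ANCOVA or mixed model appears anywhere in the article.

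Table 1 (section 2.1) ticks baseline, treatment week 4 and follow-up week 12 for all seven indicators: FBG, 2-hour postprandial glucose, HbA1c, glutathione, superoxide dismutase, malondialdehyde and 8-OHdG. Section 2.7 confirms that blood for the glucose indicators is taken both before and after treatment.

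Section 2.4 (Sample size) bases the calculation on the "mean and standard deviation of fasting blood glucose scores after 4 weeks of treatment". The values come from preliminary data: mean 5.97 (SD 1.82) with α lipoic acid and mean 7.28 (SD 2.34) without it. The error rates are given as "Set α = 0.025, unilateral test, β = 0.20". The result is that "42 participants were required for each group"; once drop-out is allowed for, "47 patients would be enrolled in each group".

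**The concern.** The trial collects a baseline value of every continuous indicator and then gives it no stated role in the comparison. A patient's starting glucose plausibly predicts glucose at week 4. The inclusion and exclusion criteria (sections 2.3.2 and 2.3.3) set no glucose range, and section 2.5 mentions no stratification by glucose. If baseline is predictive, leaving it out makes the standard error larger than it needs to be in a trial of 47 per arm.

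The second part concerns the target of the analysis. A t test compares means, while a Mann–Whitney test compares ranks. Section 2.10 lets the shape of the distribution choose between them and does not say which indicators go which way. It is therefore not fixed in advance what quantity is being compared. If the Mann–Whitney branch is taken, the P value no longer refers to the means that are reported or to the mean difference on which the trial was sized.

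At stake are precision and a clearly fixed target. The validity of the trial is not in question.

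**Working it through.** **Inputs from section 2.4.** Week-4 FBG 5.97 (SD 1.82) against 7.28 (SD 2.34); one-sided α 0.025; β 0.20; 42 evaluable per group; 10% drop-out. Section 2.5 gives 1:1 allocation.

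**Input not in the article.** The correlation r between baseline and week-4 FBG. I assume 0.3 to 0.7, the same in both arms, and also show lower values.

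**Step 1: reproduce the plan's figure.**
- Difference = 7.28 − 5.97 = 1.31.
- Pooled SD = √[(1.82² + 2.34²)/2] = 2.096.
- Standardised difference = 1.31/2.096 = 0.625.
- SE at 42 per group = 2.096 × √(2/42) = 0.457; noncentrality = 1.31/0.457 = 2.86.
- Noncentral t power for an unadjusted two-sample t test: 79.8% at 41 per group and 80.8% at 42 (Welch version at 42: 80.7%). The requirement is therefore 42.
- Drop-out: 42/0.90 = 46.7, rounded up to 47.

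The stated 42 and 47 reproduce with an unadjusted t test on raw week-4 values. Sections 2.4 and 2.10 agree with each other, and this supports raw follow-up values as the likely reading of section 2.10.

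**Step 2: adjust for baseline.** Under ANCOVA the residual SD is 2.096 × √(1 − r²), with one degree of freedom fewer (81). At 42 per group:

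| r (assumed) | Variance reduction r² | SE | Power | n per group for 80% |
|---|---|---|---|---|
| unadjusted | – | 0.457 | 80.8% | 42 |
| 0.1 | 1% | 0.455 | 81.2% | 41 |
| 0.2 | 4% | 0.448 | 82.3% | 40 |
| 0.3 | 9% | 0.436 | 84.3% | 38 |
| 0.5 | 25% | 0.396 | 90.4% | 32 |
| 0.7 | 49% | 0.327 | 97.7% | 22 |

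At r = 0.5 the gain in precision equals that of 42/(1 − 0.25) = 56 unadjusted patients per group.

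**Step 3: if change from baseline was meant.** With equal SDs at the two times, the SD of a change is 2.096 × √[2(1 − r)]. Noncentral t power at 42 per group is 66.7%, 80.8% and 95.5% for r = 0.3, 0.5 and 0.7. ANCOVA is better at each value. Change scores do worse than the unadjusted comparison when r is below 0.5 and equal it at 0.5. The recommendation therefore does not depend on which variable section 2.10 intends.

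**Step 4: does the test switch distort type I error?** Trials with 42 per group and no treatment effect were simulated, 4,000 for each distribution. The t test was used when Shapiro–Wilk did not reject normality in either arm, and Mann–Whitney otherwise. Two-sided rejection rates were 4.9% (normal), 4.85% (lognormal) and 4.7% (gamma), against a nominal 5%. The switch does little to the error rate.

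**The case against.** **The document does not say all of this outright.** Section 2.10 does not name the analysed variable and describes no normality pre-test. Allocating tests to indicators in advance is not excluded. This stands: raw values are an inference from section 2.4. But no such allocation is given, and Step 3 shows that adjustment is preferable under either reading.

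**Nothing is invalid.** The trial is randomised 1:1, the unadjusted comparison is unbiased on average, and sample size and analysis are consistent. This stands in full. A reader might infer that the trial is underpowered. It is not: the planned 80% is met, and the loss is only relative to a better analysis of the same data.

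**Chance imbalance is not a separate harm.** A reader might infer that baseline imbalance biases the result. With r = 0.5 and a baseline SD equal to that at week 4, a 1-SE imbalance moves the unadjusted difference by 0.5 × 0.457 = 0.229, which is 17% of 1.31. But 0.396² + 0.229² = 0.157 + 0.052 = 0.209 = 0.457². The shift is the very part of the variance that the unadjusted standard error already contains. Counting it beside the wider interval counts one loss twice.

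**The size is uncertain.** The correlation is assumed, and the common diet and glucose control in section 2.6 could weaken it. The figures cover FBG only; the article gives no data from which to size the gain for the other six indicators. This stands too.

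**A statistical analysis plan may supply covariates.** Possibly, but the article is not silent here. It names the tests, so the point concerns a stated choice. How effect estimates and intervals are to be reported is fairly left to such a plan, and its absence is not held against the article.

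**Conclusion.** The point holds as an improvement worth making. The unadjusted analysis in section 2.10 is sound and delivers the planned power, but it makes no use of baseline data that the trial collects anyway. For FBG at 42 per group, adjustment would raise power from 81% to 84%, 90% or 98% at correlations of 0.3, 0.5 or 0.7, and by under two percentage points at 0.2 or below. These figures rest on the article's means and SDs and on the assumed correlation.

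The switch between tests is a lesser point. A reader might infer that it inflates false positives, but the simulation shows no inflation. Its cost is that the choice between a mean difference and a rank comparison is left to the data.

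**What to change.** In section 2.10, replace the distribution-dependent rule with one prespecified analysis for each continuous indicator:

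- ANCOVA of the week-4 value and of the week-12 value, or one mixed model for both, on treatment with that indicator's baseline value as covariate.
- Report the adjusted difference between groups with its 95% CI.
- List by name, before unblinding, any indicator to be analysed on the log scale. Choosing the log scale after seeing skewness would repeat the problem being removed.
- Keep Mann–Whitney as a sensitivity analysis only.

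This needs no extra patients, visits or assays, and SPSS 22.0, the package named in section 2.10, can fit these models. The sample size can stay as it is, since the correlation is unknown. The cost is a change of protocol wording, which section 2.9 sends back to the ethics committee for approval.

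### No outcome is designated primary: one unadjusted P < .05 rule covers seven co-equal indicators at two times and is not tied to fasting glucose at 4 weeks, the only variable used to size the trial

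*Protocol article*

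**What the plan says.** All references are to the protocol article.

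- **Section 2.7 (Outcomes)** groups the efficacy measures under two headings without ranking them. The blood glucose measures are described as "including fasting blood glucose, 2 hours postprandial blood glucose and glycosylated hemoglobin". The oxidation assays are used "to detect serum glutathione, superoxide dismutase, malondialdehyde, and 8-hydroxydeox-yguanosine". That makes seven indicators. None is called primary or secondary here or elsewhere in the article.
- **Table 1** ticks all seven at baseline, at week 4 of treatment and at week 12 of follow-up. The text of section 2.7 says of the follow-up period that "the research assistants will collect data information based on the above indicators at week 4 and week 12 after treatment".
- **Section 2.4 (Sample size)** rests on FBG alone: "The sample size is estimated based on the mean and standard deviation of fasting blood glucose scores after 4 weeks of treatment". Alpha is 0.025 one-sided and power is 80%.
- **Section 2.10 (Statistical analysis)** gives one pair of tests for continuous measures, "independent sample *T* test will be used for normal distribution, and Mann–Whitney *U* test will be used for skewness distribution", and one threshold: "The difference is considered statistically significant when" P is below .05. It sets no order among outcomes or times and makes no reference back to FBG.

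**The concern.** The planned error rate belongs to one comparison, FBG after 4 weeks. The stated decision rule belongs to every comparison. Nothing in sections 2.7 or 2.10 says which result decides the trial. If FBG showed no difference and, say, malondialdehyde at follow-up week 12 gave P = .04, the plan as written would call that a significant effect with the same standing as FBG.

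This matters because the Introduction and Discussion justify the trial by the lack of rigorous randomised evidence for the combination, and the Abstract offers the result as a reference for clinical use. A claim of that kind needs an error rate that is fixed before the data are seen.

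**Working it through.** **1. The plan's own figure.** Inputs from section 2.4: 5.97 (SD 1.82) against 7.28 (SD 2.34), one-sided 0.025, power 0.80, dropout 10%.

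- Difference: 7.28 − 5.97 = 1.31.
- Pooled SD: √[(1.82² + 2.34²)/2] = √4.394 = 2.096.
- Normal approximation: n = 2 × (1.960 + 0.842)² × 4.394 / 1.31² ≈ 40.2, so 41 per group.
- Noncentral t: power is 0.798 at 41 and 0.808 at 42, so 42 per group.
- Dropout: 42 / 0.90 = 46.7, so 47 enrolled per group.

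The stated 42 and 47 reproduce. One-sided 0.025 and two-sided 0.05 give the same n. The sample size is not part of the problem.

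**2. Number of comparisons.** On the Table 1 schedule: 7 indicators × 2 post-baseline times = 14.

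**3. Independent tests, no true effect.** Section 2.10 does not state sidedness; P < .05 is read here as two-sided, so each test has a 2.5% chance of a false result in favour of α lipoic acid.

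- At least one P < .05 in either direction: 1 − 0.95^14 = 0.512.
- At least one in favour of α lipoic acid: 1 − 0.975^14 = 0.298.

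**4. Correlated tests.** The article gives no correlations, so these are assumed values, simulated with 400,000 draws of 14 normal test statistics. The correlation between times is 0.5.

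| Correlation between outcomes | Any P < .05 | In favour of α lipoic acid |
|---|---|---|
| 0 (and 0 between times) | 51% | 30% |
| 0.3 | 44% | 23% |
| 0.5 | 38% | 19% |
| 0.7 | 30% | 15% |

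Two other assumed structures test how far this depends on the choice:

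- One common correlation among all 14 statistics gives 44%, 35%, 25% and 14% in either direction at 0.3, 0.5, 0.7 and 0.9. In favour of α lipoic acid the figures are 22%, 17%, 12% and 7%.
- A block structure (0.6 within glycaemic, 0.4 within oxidation, 0.2 between the groups, 0.5 between times) gives 43% and 22%.

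**5. Other counts.**

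- Treatment week 4 only, 7 tests: 1 − 0.95^7 = 30% if independent, and 27% to 18% at outcome correlations 0.3 to 0.7. In favour of α lipoic acid: 16% if independent, and 14% to 9%.
- If section 2.7 is read as adding a follow-up week-4 measurement, there are 7 × 3 = 21 tests: 1 − 0.95^21 = 66% if independent.

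**6. With one declared primary.** FBG at the end of treatment, tested alone at two-sided 0.05, has a type I error of 5% and power 0.808 at 42 per group. For contrast, giving all 14 equal confirmatory standing under Bonferroni means 0.05/14 = 0.00357 per test. FBG power at 42 per group would then be about 0.45, and about 73 evaluable per group would be needed (normal approximation). That is the price of keeping 14 co-equal outcomes; it does not measure the present defect.

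**The case against.** The best counter-argument is that FBG after 4 weeks is already the lead outcome in practice, because the trial is sized on it and on nothing else. Promoting another marker would visibly depart from the published basis for the sample size. That stands as far as it goes: what is missing is the label and the link to the conclusion, and a reader who infers an entirely free choice among 14 results goes too far. But the sizing variable does not limit a significance rule that section 2.10 applies to every difference.

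A second argument is that this is a condensed article, and that adjustment methods and the ordering of secondary outcomes are commonly left to the full protocol or SAP. This also stands in part. The absence of an adjustment method is not charged here. The point is what the article does state: co-equal outcomes and one threshold for all of them.

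Third, the count of 14 is an inference. Table 1 is a measurement schedule, section 2.10 does not list which times are tested, and the timing in section 2.7 can be read differently. The count should be taken as the Table 1 reading.

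Finally, a reader might infer that a false-positive claim is more likely than not. The figure passes one half only when the 14 tests are close to independent. At the assumed outcome correlations of 0.3 to 0.7 it is below that, and for a false claim of benefit it stays at or below 30% on the 14-test count.

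**Conclusion.** The point holds in this form: no outcome is designated primary, and the P < .05 rule is not tied to the variable that sizes the trial. On the Table 1 reading of 14 two-sided comparisons with no true effect, the chance of at least one nominally significant result is 51% under independence and about 30% to 44% at assumed outcome correlations of 0.7 to 0.3. For a false result in favour of α lipoic acid it is 30% and about 15% to 23%. Even a common correlation of 0.9 leaves 14% in either direction, nearly three times the nominal 5%.

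The correlations are assumptions and the count depends on how the visit schedule is read. The direction of the finding depends on neither. The documents support an error rate several times nominal; they do not show that a false claim is probable.

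**What to change.** In sections 2.7 and 2.10:

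- Name FBG at the end of the 4-week treatment period as the single primary outcome, tested at two-sided 0.05. In the favourable direction this equals the planned one-sided 0.025. State that the trial's conclusion rests on it.
- Label the other six indicators, and all follow-up week-12 comparisons, as secondary or exploratory, and state that an unadjusted P < .05 on any of them supports no confirmatory claim. A Holm correction, or estimates with 95% confidence intervals, are reasonable options; neither is required.
- Align the measurement times in section 2.7 with Table 1, so that the set of comparisons is unambiguous.

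The cost is wording only, provided that it is done before the data are seen. The sample size stays at 42 evaluable and 47 enrolled per group, and FBG power stays at about 81%. What is given up is stand-alone significance claims on the other markers.
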